### **Statistical Analysis**

The use of randomization by clusters conditions the statistical analysis that can be employed, especially in the calculation of confidence intervals and the testing of hypotheses. The following analyses will be undertaken:

1. **Descriptive analysis** of each variable with its corresponding CI at 95 %. Description of the profile of patients who abandoned the study plus their reason for withdrawal.

2. **Baseline comparison** of the two intervention groups in terms of the variables measured, prognostic factors and descriptive variables. Bivariate statistical tests will be used depending on the type of variable (qualitative or quantitative one).

3. **Analysis of primary outcome**: comparison of the proportion of patients that improve in 4 or more points in the area of Mental Healthcare from the SF-12 in both groups, at 12 months after patient inclusion, using the Chi-squared test, and the calculation of confidence intervals 95 %. Logistic regression with random effects will be used to adjust for prognostic factors; the dependent variable will be the improvement or not in 4 or more points obtained in Mental Healthcare; and the independent variable the intervention group to which each patient belonged. Confounding factors or factors that might alter the effect recorded will be taken into account in this analysis.

4. **Analysis of secondary outcomes variables**. The results of the secondary variables according to the assigned group will be compared for each secondary response variable using appropriate statistical tests.

All statistical tests will be performed with intention to treat. The last observation carried forward will be used for missing data. Significance was set at p < 0.05. All calculations will be made using SPSS© v.18 software.

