#### ***Sample size***

##### *Method of calculation*

For an alpha of 0.05, a power of 80 %, and in order to detect an increase of 20 % in the proportion of patients that improve at least 4 points on area of mental healthcare of the SF-12 questionnaire (50 % in the intervention group and 30 % in the control group), the overall sample size required is 206 patients (103 in each arm of the study).

Since randomization is by clusters, the sample size had to be larger than if simple randomisation had been performed, in order to take into account the design effect. The intra-class correlation coefficient is 0.01 
[25,26] and a mean cluster size is assumed to be 8 patients. The design effect is 1.07. Given these assumptions, and expecting a 10 % loss rate at one year, the final sample size required is 242 (121 in each arm).

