## **Discussion**

Resolute treatment of psychological or psychosocial issues by primary care professionals is a encouraging challenge. The study incorporates the PRIME MD questionnaire, a useful tool for diagnosing comorbid conditions. The time for application is 10 minutes. Its sensitivity and specificity make it a valid tool for the diagnosis of the most prevalent psychiatric disorders in primary care.

The study design used in this work is, however, subject to certain limitations. The intervention cannot be masked, which could influence the assessment of its effect. Certainly, the possibility of contamination exists if the patients or professionals involved communicate with one another. For this reason randomization by clusters was employed. It was assumed that the number of clusters was sufficient for the random assignment of PHCCs to one arm or the other to compensate for such potential confounding factors.

To mask the analysis of data, the persons charged with this task were blind to the arm to which each health care center had been assigned.

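### The chi-squared test of the 4-point SF-12 mental responder is unadjusted, the logistic model does not specify the baseline score as a covariate, and no analysis of the 12-month score is planned

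*Protocol article*

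**What the plan says.** Item 3 of the Statistical Analysis section of the protocol article defines the primary analysis as a "comparison of the proportion of patients that improve in 4 or more points in the area of Mental Healthcare from the SF-12" between the arms at 12 months, by chi-squared test with a 95% confidence interval. A logistic regression with random effects follows, to adjust for prognostic factors. Its dependent variable is the same responder indicator, and the only explanatory variable named is "the independent variable the intervention group to which each patient belonged". Confounders and effect modifiers are to be considered, but none is listed.

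Table 4 has the SF-12 completed at recruitment (V0) and again at the baseline visit (V1), both before the group sessions. The Variables section makes the 12-month outcome the responder only. Its secondary list adds SF-12 quality of life at 3 and 6 months, but no 12-month score. The Aims section speaks more generally of improving quality of life measured by the SF-12 at one year.

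On balance between the arms, the Discussion says that "It was assumed that the number of clusters was sufficient for the random assignment of PHCCs to one arm or the other to compensate" for potential confounders. Fourteen centres, seven per arm, are allocated by a simple random sequence.

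**The concern.** A responder defined by change depends on where the patient started. With regression to the mean, patients with low scores tend to rise and those with high scores have less room to do so. The starting score is therefore one of the strongest available predictors of the primary outcome.

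The chi-squared test cannot use it, and the model that could use it does not say that it will. With seven centres per arm and no stratification, moderate chance differences in mean baseline score are quite possible. Without adjustment they feed into the difference in responder rates.

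Cutting the score at 4 points also discards information, and no planned analysis of the 12-month score recovers it. At stake are precision, and an estimate that readers can interpret if the arms happen to start apart.

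**Working it through.** **Inputs from the document (Sample size, Randomisation).** "For an alpha of 0.05, a power of 80" per cent; responder rates "50 % in the intervention group and 30 % in the control group"; a total of 206 before inflation, that is 103 per arm; for clustering, "The intra-class correlation coefficient is 0.01", with 8 patients per centre on average; design effect 1.07; 10% loss; final size 242; 14 centres.

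**Assumptions, because the document gives no figure.** Normal scores with equal SDs; SD 10; baseline-to-12-month correlation r of 0.4 to 0.6 (0.3 to 0.7 for the score analysis). An ICC of 0.05 is used only as a sensitivity value.

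**1. The plan's own figure.**
- n per arm = [1.96·√(2·0.4·0.6) + 0.842·√(0.5·0.5 + 0.3·0.7)]² / 0.2² = 93.0.
- With continuity correction, (93/4)·[1 + √(1 + 4/(93·0.2))]² = 102.8, so 103 per arm and 206 in total, as stated.
- Design effect 1 + 7·0.01 = 1.07; 206·1.07 = 220.4; 220.4·1.1 = 242.5, against the stated 242.

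The sample size is coherent with the responder endpoint.

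**2. How strongly baseline drives the responder.**
- SD of change = 10·√(2(1−r)), which is 10 at r = 0.5. The correlation between baseline and change is −√((1−r)/2), or −0.5 at r = 0.5.
- If control patients start 2 points higher, their expected change falls by 2(1−r). At r = 0.5 that is 1 point. A 30% rate sits at z = −0.524, which moves to −0.624, and Φ(−0.624) = 26.6%. The range over r = 0.4 to 0.6 is 26.3% to 27.0%, with no treatment effect at all.
- A 3-point difference at r = 0.5 gives Φ(−0.674) = 25.0%.

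**3. How likely such a difference is.**
- Analysed per arm: 121·0.9 = 108.9, or 15.6 per centre.
- Design effect 1 + 14.56·0.01 = 1.146; effective size 108.9/1.146 = 95.1 per arm.
- SE of the baseline difference = 10·√(2/95.1) = 1.45.
- P(difference above 2 points in either direction) = 16.8%; above 3 points, 3.9%.

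**4. Gain from adding baseline to the logistic model.** Ignoring clustering, unadjusted power is Φ(0.2/√(0.46/108.9) − 1.96) = Φ(1.12), about 87%. Simulation at r = 0.5, also without clustering, gives about 91% once baseline is in the model, a gain of roughly 4 percentage points.

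**5. What a score analysis would add.**
- If change is normal, 50% against 30% corresponds to z(0.5) − z(0.3) = 0.524 SD of change.
- n per arm = 2·(1.960 + 0.842)²/0.524² = 57.1, so 58 against 93, or 38% fewer.
- Baseline adjustment multiplies the variance by (1+r)/2, giving 38, 43 and 49 per arm at r = 0.3, 0.5 and 0.7.

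Approximate power with 14 centres, from a t test on 12 degrees of freedom:

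| ICC (same on both scales) | Responder | Change score | Baseline-adjusted score, r = 0.5 |
|---|---|---|---|
| 0.01 | 75% | 91% | 97% |
| 0.05 (assumed) | 58% | 77% | 88% |

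At ICC 0.01 the noncentrality is 0.2/√(0.46/95.1) = 2.88 for the responder and 0.524/√(2/95.1) = 3.62 for the change score.

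The table is generous to the score. If the ICC belongs to the binary outcome, the ICC of the underlying score is larger. Responder against change-score power is then about 75% and 89% at 0.01, and 58% and 67% at 0.05.

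**The case against.** A reader might infer that the plan leaves baseline out of the model. The text does not say so. It provides for adjustment for prognostic factors and confounders without naming them, and baseline SF-12 could be among them. A condensed article may also leave the covariate list to a fuller document. That stands, and it limits the point on the model to the covariate not being specified. It does not touch the chi-squared test, which has no covariates, or the outcome list, which gives the SF-12 at 3 and 6 months and leaves the 12-month score out.

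A reader might also infer that the bivariate baseline tests choose the covariates. Items 2 and 3 of the Statistical Analysis section are separate, and nothing links them.

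The responder endpoint is used consistently in the Abstract, Sample size, Variables and Statistical Analysis sections, and the sample size matches it. On the plan's own inputs (121·0.9/1.07 = 101.8 effective per arm) its power is 83.5%. A broadly worded aim made operational as a responder is no contradiction.

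Chance imbalance under randomisation is sampling variation, which a test that respects clustering allows for; it is not bias. A shift of 3 to 4 percentage points is also modest against the 20-point target. Both remarks are right, and they make this a matter of precision and interpretability.

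Finally, the gain from 75% to 91% cannot be credited to a primary analysis that remains a responder analysis. Dichotomising loses information at any number of clusters; 14 centres only leave less margin.

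**Conclusion.** The point holds as a worthwhile improvement at little cost. The chi-squared comparison is unadjusted, the logistic model does not specify the baseline SF-12 mental score, and no analysis of the 12-month score is described, although every value needed is collected.

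For the responder analysis the gain from naming baseline is roughly 4 percentage points of power, under assumed normality and r = 0.5 and without clustering. Adjustment also guards against a 2-point chance baseline difference (about 17% likely at SD 10 and ICC 0.01) moving a 30% rate to 26–27%. The larger gain, about 75% to 91% or more at ICC 0.01 with 12 degrees of freedom, applies only to the supporting score analysis, and it shrinks if the ICC is higher on the score scale. SD, correlation and any ICC above 0.01 are assumptions.

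The document does not support saying that baseline is excluded, that the endpoint contradicts the aim, or that the result would be biased.

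**What to change.** Keep the 4-point responder as the primary endpoint and make three changes of wording:

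- Make the random-effects logistic model the primary inference, with arm and the baseline SF-12 mental score as a prespecified covariate. State whether baseline means V0 or V1, and use the same value to define the 4-point improvement.
- Report the standardised risk difference from that model beside the odds ratio.
- Prespecify, as the first supporting analysis, a mixed model of the 12-month SF-12 mental score with baseline score, arm and a random intercept for centre, and report the mean difference with its interval.

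No new data or visits are needed. The costs are that the adjusted odds ratio is conditional on baseline, which is why the standardised risk difference is needed, and that there is one more supporting analysis to report.

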## **Methods/Design**

### **Design of the study**

This study is a community, parallel clinical trial, randomised by clusters, that compares cognitive-behavioral intervention group with routine clinical practice. The intervention will be carried out by health professionals in 14 Primary Health Care Centres (PHCCs), in Madrid (Spain).

The randomization units will be the PHCCs (clusters). The units of analysis will be the patients between 18 and 65 years old with MUS who have seeked medical attention in PHCCs at least 10 times over the past year. The design by clusters minimised possible contamination effects between centres.

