#### ***Randomisation***

The randomization unit will be the PHCC. An independent statistician will randomly assign the 14 PHCCs (7 centres in each group) to either the intervention group or a control group following a simple, computer-generated random sequence (Epidat 3.1 software).

Consecutive patients will be chosen to minimize the risk of bias in their selection.

During consultations, patients will be informed about the study and asked whether they would like to take part. Those who accept will be asked to give their signed consent, and checks were made to ensure they met all inclusion criteria but no exclusion criteria.

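### The first-named primary test and confidence interval carry no stated adjustment for centre randomisation, and the plan does not say whether they or the random-effects model decide the trial

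*Protocol article*

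**What the plan says.** All references are to the protocol article.

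- **Randomisation.** An independent statistician will "randomly assign the 14 PHCCs (7 centres in each group").
- **Design of the study.** Centres are randomised, but "The units of analysis will be the patients between 18 and 65 years old with MUS".
- **Sample size.** The calculation allows for clustering: ICC 0.01, mean cluster size 8, design effect 1.07, final total 242.
- **Statistical Analysis, opening sentence.** "The use of randomization by clusters conditions the statistical analysis that can be employed", with intervals and hypothesis tests singled out.
- **Statistical Analysis, item 3 (primary outcome).** The proportions improving by 4 or more points are compared "at 12 months after patient inclusion, using the Chi-squared test, and the calculation of confidence intervals" at the 95% level. The next sentence reads: "Logistic regression with random effects will be used to adjust for prognostic factors". In that model the outcome is improvement or not, and the independent variable is the allocated group.
- **Abstract, Methods/design.** The order is the same: a comparison of percentages is the main effectiveness analysis, and the random-effects model is for prognostic adjustment.

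The significance level is 0.05. No order of precedence is given between the two analyses in item 3.

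**The concern.** A Chi-squared test on patients, and the usual interval that goes with it, treat every patient as an independent observation. Here whole centres are allocated, and the sample size section itself assumes that patients within a centre are correlated. The first-named primary test therefore does not match the design or the planning assumption.

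The random-effects model could repair this. As written, however, it is not given primary status and the centre is not named as its random unit. Item 3 can therefore yield two p-values for the primary outcome. The trial could be reported as positive on the Chi-squared test when the clustered model does not agree, and the published interval could be too narrow.

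**Working it through.** **Inputs from the Sample size and Randomisation sections:** 50% v 30%, alpha 0.05, power 80%, ICC 0.01, cluster size 8, 10% loss, 14 centres.

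**Step 1. Reproduce the plan's figure.** Two proportions, two-sided 0.05, 80% power:

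- 103 per arm with continuity correction (93 without).
- Design effect = 1 + (8 − 1) × 0.01 = 1.07.
- 2 × 103 × 1.07 × 1.10 = 242.5, which matches 242.

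**Step 2. Patients per centre.** 242 / 14 = 17.3. After 10% loss, 17.3 × 0.9 = 15.6. Both exceed the assumed 8. That discrepancy is a separate sample-size matter, so all three sizes are shown.

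**Step 3. Error of the unadjusted test.** If the variance is understated by a factor DE, the true two-sided type I error is 2 × (1 − Φ(1.96 / √DE)), and the interval should be √DE times as wide.

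| Patients per centre | DE at ICC 0.01 | √DE | 1.96/√DE | True type I error |
|---|---|---|---|---|
| 8 | 1.07 | 1.034 | 1.895 | 5.8% |
| 15.6 | 1.146 | 1.070 | 1.831 | 6.7% |
| 17.3 | 1.163 | 1.078 | 1.818 | 6.9% |

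The interval should therefore be about 3% to 8% wider.

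**Step 4. Simulation.** Beta-binomial data, true rate 30% in both arms, 7 v 7 centres for the larger sizes and 14 v 14 clusters for size 8, with 100,000–200,000 replicates per scenario. The ICC of 0.01 is the protocol's. The values 0.02 and 0.05 are assumptions that show the range.

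| ICC | Patients per centre | Pearson | Continuity-corrected | t test on centre proportions |
|---|---|---|---|---|
| 0.01 | 8 | 5.7% | 4.2% | 4.9% |
| 0.01 | 15.6 | 6.9% | 5.0% | 5.0% |
| 0.01 | 17.3 | 7.0% | 5.3% | 5.0% |
| 0.02 (assumed) | 15.6 to 17.3 | 8.6% to 8.9% | 6.4% to 6.9% | 4.9% to 5.0% |
| 0.05 (assumed) | 15.6 to 17.3 | 13.9% to 14.8% | 11.1% to 12.1% | 5.0% to 5.1% |

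The t test on centre proportions (12 df with 14 centres) holds its level throughout. The Chi-squared test does so only in its corrected form, and only at about ICC 0.01.

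**The case against.** The strongest reply is that clustering is not ignored. The section acknowledges it, and item 3 contains a random-effects logistic model with treatment group as the independent variable, which does test the treatment effect on the primary outcome. That stands. A reader might infer that the plan has no clustered analysis, or that the model serves prognostic adjustment alone, and the text supports neither. The defect is narrower: an unadjusted test is named first, the random unit is not stated, and the deciding analysis is not designated.

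The second reply concerns size. It is tempting to say that the type I error must exceed 5%, or that it reaches 14%. The first depends on which Chi-squared test is used, and the protocol does not say. The planned 103 per arm reproduces only with a continuity correction, and a corrected test stays near 4–5% at ICC 0.01. The second requires an ICC that the document does not give. Even so, an interval computed without allowance for centre remains too narrow at any positive ICC, and the corrected test loses its protection as the ICC rises.

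Three further extensions should not be pressed:

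- Extra correlation from treating patients in groups of 6–12 is plausible, but the document gives no figure for it.
- Poor small-sample behaviour of the random-effects model's own Wald test was not examined here.
- The wording for secondary outcomes, which "will be compared for each secondary response variable using appropriate statistical tests", is vague but not wrong, and such detail is commonly left to the analysis plan.

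Deferral to an analysis plan does not answer the main point, because the article names a specific test for the primary outcome.

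**Conclusion.** The point holds in a limited form. The first-named primary test and interval do not match a design with seven centres per arm, and the plan does not say which of its two analyses decides the trial. At the protocol's own ICC of 0.01 the consequence is modest: a type I error of 5.8% to about 7% for an uncorrected Pearson test, about 4–5% with continuity correction, and an interval that should be 3–8% wider. Larger errors (about 9% at ICC 0.02 and 14–15% at 0.05, uncorrected) rest on assumed ICCs.

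These figures assume a two-sided test, roughly equal centre sizes and no adjustment beyond what item 3 states. The case for correction rests mainly on the contradiction within the section and on the open choice between two p-values, and less on the size of the inflation.

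**What to change.** In item 3, name one centre-adjusted analysis as primary. Two options are suitable:

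- the logistic model with a random intercept for centre, tested against a small-sample reference suited to 14 clusters (for example t on 14 − 2 = 12 df); or
- a t test on the 14 centre proportions.

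Report the effect with a centre-adjusted 95% interval. Drop the unadjusted Chi-squared test or label it descriptive. Make the abstract agree.

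**Cost.** This is a change of wording and needs no new data. The interval widens by 3–8% for clustering at ICC 0.01, and a 12-df reference widens it by a further factor of 2.179 / 1.960 = 1.11. For 50% v 30% with 15.6 analysed patients per centre, the half-width goes from 12.7 to 15.2 percentage points. Approximate power is then about 75%, against about 81% for a normal approximation that allows for the same clustering. The sponsor should know this before choosing.

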### **Data collection method**

The doctor will recruit the patients and will assess the selection criteria. He will let the patient know about the objectives of the study; and will request his informed consent.

All patients who accepted to participate will get the SF-12 questionnaire on quality of life at the end of the doctor’s examination. Furthermore, all patients will get the PRIME-MD questionnaire to identify any psychiatric co-morbidity that will be treated by the doctor according to his criterion.

At 3, 6 and 12 months (visits V2, V3 and V4, respectively) will be referred the patient to evaluate the usefulness of cognitive-behavioral sessions, and completion of quality of life questionnaire (SF-12) and Clinical Global Impression of patient and physician (PGI and CGI).

The structure of the study is described in Table 
4.

**Table 4 T4:** Project structure

	**Intervention Group**	**Control Group**
**Recruitment visit (V 0)**	Selection criteria	
Consecutive selection	Request on informed consent	
	PRIME MD Questionnaire	
	Variables:	
	· SF-12 Questionnaire on life quality	
	· Descriptive variables: sex, cultural level, age, months with symptoms, time on antidepressants consumption, requested tests y specialized derivations to	
**Training of professionals involved**	Training in management of PRIME-MD survey. Review of Standards of Good Clinical Practice	
	Training in cognitive-behavioral (Only intervention Group)	
**Baseline visit (V1)**	Variables:	
	· SF-12 Questionnaire	
	· Prescribed medicine	
	· Requested tests	
	· Derivations to secondary level	
	· Days of sickness absence	
	· Assessment of compliance with the standards of good clinical practice	
	· Questionnaire on global clinical impression; both, the doctor and the patient	
**Intervention**	There will be a weekly group session for 4 weeks (Only intervention Group)	
	Routine clinical practice	
**3-months post Intervention visit (V2)**	Variables:	
	· SF-12 Questionnaire	
	· Prescribed medicine	
	· Requested tests	
	· Derivations to secondary level	
	· Days of sickness absence	
	· Assessment of compliance with the standards of good clinical practice	
	· Questionnaire on global clinical impression; both, the doctor and the patient	
	· Assessment by the nurse subject participation.	
	· Assessment of cognitive- behavioral module by subject (Only intervention Group)	
**6-months post Intervention visit (V3) 12-months post Intervention visit (V4)**	Variables:	
	· SF-12 Questionnaire	

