### **Variables**

#### ***Outcomes variables***

The main outcome variable is the improvement in 4 or more points in the area of Mental Healthcare from the SF-12 Quality of life at 12 months. The Spanish version of this Questionnaire has been validated: high inner consistency (range 0.77-0.92) for all the dimensions, except social function (0.55). The questionnaire is self-administered.

The secondary outcome variables recorded are:

– Questionnaire on Global Clinical Impression. Used to assess the patient's (PGI questionnaire) and the doctor’s (CGI Questionnaire) perceptions on the its improvement with the interventions. Will be administered at 6 months (to assess the effectiveness of the rules of good clinical practice) and at 12 months to evaluate the effectiveness of the intervention group added to the standards of good clinical practice. Will be treated as ordinal qualitative variable.

– Quality of life at 3 and 6 months after the intervention measured by the SF-12 questionnaire.

– Number of consultations during the period of study (broken down between nursing and medicine, each group session will be counted as a nursing consultation).

– Prescribed medicine during the period of study, with doubtful therapeutic value for their processing; related to the MUS. The included medicines are those related to the functional symptomatology:

– Pain: analgesic medicines, Nonsteroidal Anti-inflammatory Drugs and muscular pain reliever.

– Dizziness: vestibular sedatives, peripheral brain and vasodilators.

– Digestive Symptoms: pro-kinetics, anti-emetics.

– Asthenia: vitamin complex, restoratives, derived from ginseng, appetite stimulants.

– Anxiety: anxiolytics, antidepressants.

It will be regarded as quantitative variable, defined as the number of medicine taken during the period of study.

– Days of sickness absence during the period of study.

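### Last observation carried forward is the article's only missing-data rule, so 12-month SF-12 response is scored from earlier visits; the bias has unknown direction and is probably small at 10% loss

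*Protocol article*

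**What the plan says.** The final paragraph of Statistical Analysis states "All statistical tests will be performed with intention to treat" and then "The last observation carried forward will be used for missing data". It exempts no outcome, visit or reason for missingness.

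The endpoint is defined under Outcomes variables, where the sentence ends by naming the one-year assessment: "The main outcome variable is the improvement in 4 or more points in the area of Mental Healthcare from the SF-12 Quality of life at". Data collection method places follow-up assessments "At 3, 6 and 12 months (visits V2, V3 and V4, respectively"), so 3- and 6-month SF-12 values exist to be carried forward. Table 4 also lists the SF-12 at recruitment (V0) and baseline (V1).

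Under Withdrawal, non-attendance at follow-up is a reason for withdrawal, and withdrawn patients stay in the intention-to-treat analysis. The sample-size section expects 10% loss at one year and gives neither its timing nor its split by arm.

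Three secondary outcomes are totals over the study. They include "Number of consultations during the period of study" and "Days of sickness absence during the period of study"; the third is the number of medicines taken.

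**The concern.** The trial asks whether four weekly sessions still benefit patients at 12 months. Quality of life at 3 and 6 months is listed separately, as a secondary outcome. Carrying forward blurs that distinction, and it makes opposite assumptions depending on when a patient leaves:

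- A patient who leaves after a good 3-month score counts as a 12-month success, on the assumption that the gain lasts.
- A patient who leaves before any follow-up counts as a failure, on the assumption that nothing changes.

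Neither assumption is argued for. Some withdrawal reasons (a newly found organic cause, outside psychotherapy) plausibly relate to outcome. Only one arm is asked to attend groups and the trial is unmasked, so unequal loss is credible, although the article gives no figures on it.

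At stake are the responder rates in the primary comparison and their precision, because each imputed value enters the test as an observation.

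**Working it through.** **Inputs from the article.** Response rates: "50 % in the intervention group and 30 % in the control group". Error rates: "For an alpha of 0.05, a power of 80" %. Design effect 1.07, loss 10%, 121 patients per arm.

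**The plan's own figure.** A two-sided test of 50% versus 30% needs

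[1.960 × √(2 × 0.40 × 0.60) + 0.842 × √(0.25 + 0.21)]² / 0.20² = 93 per arm.

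The continuity correction raises this to 103. Then 103 × 1.07 = 110.2, and 110.2 × 1.10 = 121.2, so 121 per arm and 242 in all. The stated size reproduces and is not in question.

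**Amount imputed.** 0.10 × 121 ≈ 12 patients per arm would have an imputed 12-month outcome.

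**Formula.** Observed arm rate = (1 − d) × p + d × e. Here d is the share lost, p the 12-month response in completers, and e the share of leavers whose last value shows a gain of 4 or more points. The fade, timing and unequal losses below are assumptions; the article gives none of them.

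**Case 1: no true 12-month difference (30% in both arms), intervention response 50% at 3 months fading fully to 30%, all losses just after the 3-month visit.**

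- 10% loss: 0.9 × 0.30 + 0.1 × 0.50 − 0.30 = +0.02.
- 20% loss: 0.8 × 0.30 + 0.2 × 0.50 − 0.30 = +0.04.

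**Case 2: as Case 1 with 10% loss, but one third of leavers with baseline only, one third last seen at 3 months and one third at 6 months.** Linear fade gives a 6-month response of 50 − 20 × 3/9 = 43.3%.

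- Intervention: 0.27 + 0.0333 × 0.50 + 0.0333 × 0.433 = 0.301.
- Control: 0.27 + 2 × 0.0333 × 0.30 = 0.290.
- Difference: about +0.01.

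**Scale.** The effective number per arm is 121 / 1.07 = 113. The standard error of the difference at 30% is √(2 × 0.30 × 0.70 / 113) = 0.061, about 6 points. A 2-point bias raises the two-sided error rate from 5% to about 6%; a 4-point bias raises it to about 10%.

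**Case 3: true rates 50% and 30%, losses before 3 months (e = 0), leavers would have responded like completers.**

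- 15% versus 5% lost: 0.85 × 0.50 − 0.95 × 0.30 = 0.14 instead of 0.20.
- 5% versus 15% lost: 0.95 × 0.50 − 0.85 × 0.30 = 0.22 instead of 0.20.

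Cases 1 and 3 show that the sign depends on when patients leave and from which arm.

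**Precision.** If the 10% imputed values carried no information, treating them as observed would understate the standard error by a factor of about √0.9 = 0.95, or roughly 5%.

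**Totals over the study.** The result depends on how visit entries are recorded, which the article does not say. If they are running totals at a constant rate, carrying forward from month 3 or 6 with 10% loss lowers an arm mean by 0.10 × 9/12 = 7.5% or 0.10 × 6/12 = 5%. With equal loss and timing, the ratio between arms is unchanged. With 15% versus 5% lost, the ratio becomes 0.8875 / 0.9625 = 0.92 or 0.925 / 0.975 = 0.95. If they are interval counts, carrying the last one forward projects use onward and does not stop it.

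**The case against.** The strongest reply is that the harm at the planned loss is slight. A bias of 1 to 2 points is small beside a standard error of about 6, and even that needs a complete fade. The 20% and 15%-versus-5% losses appear nowhere in the article, and the 14-point result also needs early leavers to respond like completers. The plan will describe patients who abandon the study and their reasons, so unequal loss would be visible. All of this stands and limits the size of the point. It does not make the rule a sound choice for a 12-month endpoint. Nor is this a detail left to a fuller document, because the article states the rule outright.

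A reader might infer two stronger things that the article does not support.

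- **That the rule favours the intervention.** It does so only for leavers whose last value is an early gain that later fades. Leavers with baseline only are pushed the other way. Even their exact score is uncertain: change is zero if V1 is the reference, but the SF-12 is also taken at V0 and the article does not name the reference visit.
- **That it freezes cumulative counts and makes leavers look like low users.** This holds only if visit entries are running totals. Consultations are not in the Table 4 visit list, so they may come from centre records and not be missing at all.

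Multiple imputation has limits too. It assumes that the recorded data explain the missingness, which is doubtful for patients withdrawn for an organic diagnosis or outside psychotherapy. Hence the sensitivity analyses in the fix.

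**Conclusion.** The point holds as a weakness in a stated method, and the rule should be changed. For the primary endpoint it replaces the 12-month outcome with an earlier one for late leavers, imposes non-response on patients with baseline data only, and ignores imputation uncertainty.

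The direction of bias is unknown. At the planned 10% loss the size is probably small: about +1 to +2 points under a true null, given 50% early intervention response fading fully to 30%. It grows with heavier or unequal loss, to +4 points at 20% loss or from 20 down to 14 points at 15% versus 5% early loss, under the assumptions shown. The sample size is unaffected. For the totals, the consequence is conditional on how entries are recorded and no direction can be claimed.

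**What to change.** Replace the carried-forward rule as follows.

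1. **Primary endpoint.** Multiply impute the missing 12-month SF-12 mental score separately by arm, using baseline, 3- and 6-month scores, age, sex and PRIME-MD comorbidity, and allowing for centre. Derive the 4-point response after imputation and combine the results across imputed data sets.
2. **Sensitivity analyses.** Report missing = non-response, and a shift of the imputed scores away from missing at random, varied by arm.
3. **Totals over the study.** Do not carry values forward. State whether entries are running totals or interval counts, and impute the missing intervals. Avoid a simple constant-rate follow-up offset for consultations: each group session counts as a nursing consultation and all four fall in the first weeks, so an offset would inflate the rate for early leavers in the intervention arm only.

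All the variables named are already collected. The cost is revised analysis wording, some programming (including a check that the named software can impute while allowing for centre) and slightly wider intervals. No new data are needed.
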